#### Mediators

The following a priori mediators will be tested: sexual functioning knowledge (knowledge perception and quiz questions, which were reviewed and revised by survivors of breast cancer); sexual communication self-efficacy with a health care provider (items on confidence to raise and discuss sexual concerns) [33]; sexual communication self-efficacy with partner (Self-efficacy to Communicate about Sex and Intimacy scale [54]); and emotional intimacy with partner (emotional intimacy subscale of the Personal Assessment of Intimacy in Relationships scale [55]). Mediator variables will be assessed at all 3 time points; the primary evaluation is change between baseline and 12-week assessments.

#### Moderators

The following a priori moderators will be collected or assessed at baseline: menopausal status (self-reported), use of AET (medical record extraction), time since primary breast cancer treatment completion (medical record extraction), psychological distress (Patient Health Questionnaire-4) [56], relationship duration (self-reported), and relationship satisfaction (Relationship Assessment Scale) [57]. Psychological distress and relationship satisfaction will also be measured at 12- and 24-week assessments as exploratory outcomes.

#### Engagement and Acceptability

Participants’ engagement with the SHINE intervention will be characterized by metrics including the number of log-ins and Core completion rates (collected automatically by the SHINE intervention platform). At the 12-week assessment, participants will rate their satisfaction with the SHINE intervention Cores (Client Satisfaction Questionnaire-8) [58] and perceived usability of the Cores (Internet Intervention Utility Questionnaire) [59].

#### Sample Size and Power Analysis

This factorial trial has been powered to detect a small-to-medium effect size (ie, Cohen *d*=0.30) of intervention components on sexual morbidity outcomes. This represents the smallest effect size that the study team determines would offset the required resources of an intervention component to be delivered to and completed by participants in an optimized intervention. Determined using the MOST R package [60] *FactorialPowerPlan* function (R version 3.6.2; R Foundation for Statistical Computing), 247 survivors of breast cancer would be needed to detect Cohen *d*=0.30 of change in sexual distress from baseline to 24-week assessment (measured by FSDS-DAO) at 80% power with α=.05 for all main effects and interaction effects of the intervention components. In a factorial experimental design with only 2 levels per factor, the power to detect main effects and interaction effects is equal [39,61]. This power analysis assumes a pretest-posttest correlation in sexual distress of *r*=0.65, which is supported by data from the investigators’ prior research (Female Sexual Distress Scale pretest-posttest *r*=0.73; N=28) [32] and by Female Sexual Distress Scale validation data (pretest-posttest *r*=0.62; N=318) [49]. The effect size of Cohen *d*=0.30 is reasonable to expect from intervention components, given that prior randomized controlled trials of interventions containing the components demonstrated large effects on sexual distress relative to control (Cohen *d*=0.87 and Cohen *d*=0.59) [28,32]. Conservatively accounting for an estimated 20% attrition (based on the investigators’ past trials) [32,42,62] and rounding up to achieve a balanced number of participants per condition, 320 survivors will be randomized in the trial (247/0.80=309 rounded to a total N=320, for n=20 per each of the 16 factorial conditions).

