#### Sexual Morbidity Outcomes

Two outcomes will be evaluated to determine the optimal combination of intervention components: the Female Sexual Distress Scale–Desire, Arousal, Orgasm (FSDS-DAO [48,49]; primary outcome) and the Female Sexual Function Index (FSFI [50-52]; secondary outcome). These measures will be assessed at all 3 time points (ie, baseline, 12-week, and 24-week assessments); the primary evaluation is change between baseline and 24-week assessments.

The FSDS-DAO measures sexual distress among women and will be the primary outcome of the intervention optimization decision-making process. It has established reliability, construct and discriminant validity, and sensitivity to treatment-related changes [48,49]. Participants will rate 15 items on a 5-point Likert scale from 0 (never) to 4 (always). Total sum scores range from 0 to 60, with higher scores reflecting greater sexual distress.

The FSFI measures sexual functioning among women. It also has established reliability, construct and discriminant validity, and sensitivity to treatment-related changes [50-52]. Scores will only be evaluated from women who report having sexual activity within the past 4 weeks, as recommended [53]. Participants rate 19 items on a 5- or 6-point Likert scale from 0 (eg, no sexual activity) or 1 (eg, almost never or never) to 5 (eg, almost always or always). To compute a total score, summed scores of each of the 6 domains (desire, arousal, lubrication, orgasm, satisfaction, and pain) are scaled to a maximum score of 6, which are in turn summed for the total score. Total scores range from 2 to 30, with higher scores representing better sexual functioning and a total score of ≤26.0 suggestive of clinically relevant sexual dysfunction.

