### Data Analysis Plan

#### Overview

In accordance with the NIH requirement, a Data Safety and Monitoring Plan has been established to guide study oversight and ensure the safety of participants and data validity and integrity. Summaries of primary and secondary measures will be reviewed for completeness every 6 months by the WF NCORP RB Data Safety Monitoring Board, along with other key study metrics such as recruitment, retention, patient characteristics, and adverse events. More details about trial oversight and monitoring are available in Multimedia Appendices 3 and 4.

Study methods have been designed to avoid missing data, including efforts to retain participants with incentives and assessment reminder protocols, as well as requiring responses to all items on web-based assessment questionnaires. As it is not possible to entirely avoid missing data, restricted maximum likelihood estimation will be used to address missing data in analyses under a missing at random (MAR) assumption [63-65]. Proposed analyses are robust against MAR data [63,64]. The National Academy of Sciences guidelines for missing data will be followed [64], and the impact of missing data on study conclusions will be explored with sensitivity analyses. Specifically, attrition rates across study conditions will be compared. If a particular condition has a markedly higher dropout rate, baseline covariates that predict attrition will be identified in secondary analyses. Variables determined to predict loss to follow-up will be included in sensitivity analysis models to satisfy the conditions described by Little and Rubin [65] for data to be considered MAR.

Primary analyses will be intention to treat, meaning that the randomized condition assignment will be included in models regardless of whether the participant completes their assigned Cores or not. Sensitivity analyses will examine the effects by whether assigned Cores are completed or not. All participants with at least 1 follow-up assessment will be included in analyses. All tests of hypotheses and reported P values will be 2 sided.

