#### Primary Objective Analyses

The primary objective of this study is to identify the most efficient intervention package that is expected to produce the greatest benefit to survivors’ sexual health with the fewest (and least-intensive) intervention components. This objective will be achieved using an “all-active components” optimization criterion to guide a decision-making process with systematic data analysis [39]. The main and interaction effects of components will be computed using a generalized linear model (GLM) approach to ANOVA with effect coding to compare the average change in sexual morbidity aggregated across experimental conditions [66].

A model will be conducted for effects on sexual distress, measured by the FSDS-DAO; this model will be prioritized for the intervention optimization decision-making process. First, only components (and component levels) that have a beneficial independent effect (ie, a small-to-moderate positive main effect [Cohen *d≥*0.3]) on sexual distress will be provisionally included. Next, these provisional decisions will be reviewed by examining component interaction effects. Components will be considered for addition to the intervention package if they have important (ie, Cohen *d≥*0.3) synergistic effects, meaning they amplify the benefit of another component in the package. Components will be considered for removal from the package if they have important (ie, Cohen *d≥*0.3) antagonistic effects, meaning they reduce the benefit of another component in the package. Decisions will be informed by computing parsimonious prediction models for outcomes from both the main and interaction effects of the included components [39].

A subsequent model will be conducted for sexual functioning among women reporting sexual activity within the past 4 weeks, measured by the FSFI. Model results will be compared between sexual distress (full population) and sexual functioning (sexually active population only). Components (and component levels) provisionally included based on the sexual distress model findings may be removed if there is a substantial negative effect on sexual function. While discrepant or antagonistic results between the sexual distress and sexual functioning models are possible, they are unlikely, given that FSDS-DAO and FSFI total scores have been found to be highly correlated (*r=*–0.65 [49]).

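### The d=0.30 power claim is worded for both sexual morbidity outcomes, but the calculation supports it only for FSDS-DAO, not for FSFI in the sexually active subset

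*Protocol article*

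**What the plan says.** The section on sample size and power in the protocol article opens with a claim in the plural: "This factorial trial has been powered to detect a small-to-medium effect size (ie, Cohen *d*=0.30) of intervention components on sexual morbidity outcomes". Table 2 and the section on sexual morbidity outcomes give that term its content: FSDS-DAO as primary and FSFI as secondary. The latter section introduces the pair with "Two outcomes will be evaluated to determine the optimal combination of intervention components".

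The calculation that follows concerns one of them. It says "247 survivors of breast cancer would be needed to detect Cohen *d*=0.30", continuing "of change in sexual distress from baseline to 24-week assessment (measured by FSDS-DAO", and then "at 80% power with α=.05 for all main effects and interaction effects of the intervention components". Its correlation is also specific to that outcome: "This power analysis assumes a pretest-posttest correlation in sexual distress of *r*=0.65". The only allowance for loss is 20% attrition, which takes 247 to 309, rounded up to 320.

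The primary objective analyses describe a narrower population for FSFI: "A subsequent model will be conducted for sexual functioning among women reporting sexual activity within the past 4 weeks". The same section contrasts this with the full population used for distress, and it allows a provisionally included component to be dropped if its effect on sexual function is substantially negative. Eligibility (Table 1 and the participants section) requires an intimate relationship and at least one bothersome sexual symptom attributed to breast cancer. No criterion requires current sexual activity.

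**The concern.** The opening sentence covers both outcomes, but the calculation covers one, in all retained women. FSFI comes from a subset whose size the article does not estimate. Low interest or pain during sexual activity is enough to qualify for the trial, so some participants should be expected to have no evaluable FSFI score.

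This matters because FSFI acts as a check for harm within the primary-objective decision. The study team calls d=0.30 the smallest effect worth the resources of a component. Taking the opening sentence at face value, a reader could treat an unremarkable FSFI result as coming from an analysis powered at that threshold, and so as reassurance that no component harms function.

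**Working it through.** **Inputs from the article.** d=0.30; α=.05; "All tests of hypotheses and reported P values will be 2 sided"; r=0.65 (given for distress); 320 randomised, 20 in each of 16 conditions, so 160 against 160 for every factor; 20% attrition.

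**Inputs not in the article, assumed here.** The share s of completers with an evaluable FSFI, and the FSFI pretest-posttest correlation (0.65 borrowed from distress).

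**1. Reproduce the stated number for FSDS-DAO.**
- Variance of a change score in units of the raw SD: v = 2(1 − r) = 2(1 − 0.65) = 0.70.
- Normal approximation: N = 4v(1.96 + 0.842)²/d² = 4 × 0.70 × 7.85/0.09 ≈ 244, or 246 when the standard sample-size routine is run per arm and doubled.
- Noncentral F with 1 df, noncentrality λ = N·d²/(4v) and 16 model parameters: N=247 gives 80.1% power and N=246 gives 79.96%. So 247 is reproduced exactly.
- 247/0.80 = 308.75, rounded up to 309. The next multiple of 16 is 320.
- Alternatives that do not give 247: no pretest (350 or 351) and baseline as covariate with variance 1 − r² (202 or 204). The plan's figure is therefore the change-score one.

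**2. Margin left for FSFI.**
- Expected completers: 320 × 0.80 = 256. Power at 256 is 81.5%.
- Margin over the requirement: 256 − 247 = 9 women, and 9/256 = 3.5%.
- Stated without fixing attrition: retention × s must be at least 247/320 = 0.772.

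**3. FSFI power at d=0.30 over a range of s.** Same noncentral F, N = 256 × s, v = 0.70:

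| Evaluable share s (assumed) | N | Power at d=0.30 | Detectable d at 80% power |
|---|---|---|---|
| 95% | 243 | 79.5% | 0.30 |
| 90% | 230 | 77% | 0.31 |
| 80% | 205 | 72% | 0.33 |
| 70% | 179 | 66% | 0.35 |
| 60% | 154 | 60% | 0.38 |
| 50% | 128 | 52% | 0.42 |

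**4. Sensitivity to the borrowed correlation and to the model.**
- With r=0.50 (v=1.0), power is 57% at s=80% and about 46% at s=60%. With r=0.80 (v=0.40), it is 92% and 83%.
- The FSFI correlation that would restore 80% power is about 0.71 at s=80% and about 0.78 at s=60%.
- With baseline as a covariate and r=0.65, about 204 evaluable women suffice, and 204/256 is about 80%.

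**The case against.** Four points weigh on the other side.

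First, the article never states 80% power for FSFI. The 80%, the correlation and the supporting effect sizes all concern sexual distress, and the opening sentence gives a target d without a power level. A reader might infer from the plural that 80% power is claimed outright for FSFI. The text does not go that far. What remains is that the sentence says the trial was powered at d=0.30 for outcomes that the article itself defines as two.

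Second, FSFI is secondary. It need not be powered, the distress model is expressly given priority, and the restriction to sexually active women is disclosed. An article may also leave power for a secondary outcome to the full protocol or analysis plan. All of this stands. The point is not that an FSFI power figure is missing, but that the article makes a claim wider than its calculation.

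Third, a reader might infer that FSFI change exists only for women active at both baseline and 24 weeks. The article does not fix the visits. It plans restricted maximum likelihood under MAR and includes every participant with at least one follow-up assessment, so some women missing one score may still contribute. The calculation above therefore uses an evaluable share and does not assume activity at both visits.

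Fourth, the shortfall is conditional. The activity share is unknown and the correlation is borrowed. A higher correlation, attrition well under 20% or baseline adjustment could bring FSFI to 80%. That stands, and it is why the table is illustrative. None of these features is in the stated calculation.

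It is also fair to say that FSFI's role is a discretionary judgement about the size of a negative effect, with no rule that reads a null result as support for a component. That limits the harm but does not remove it, because an imprecise harm check is easier to over-read when the plan calls it powered.

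**Conclusion.** The point holds as a matter of scope. The sample size is right for FSDS-DAO, and nothing here shows that the trial is too small for its primary outcome or that more women are needed. The power statement is too wide: on the plan's own d, α, r and attrition, FSFI stays at 80% only if at least about 96.5% of completers are evaluable (247/256). The article gives no basis for that share, and eligibility does not secure it.

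How far power falls cannot be read from the documents. About 72% to 52%, for evaluable shares of 80% to 50%, is an illustration that rests on r=0.65 borrowed from distress, 20% attrition and a change-score analysis. That FSFI is certainly underpowered is a stronger conclusion than the documents support.

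**What to change.** In the sample-size section, replace the reference to sexual morbidity outcomes in the opening sentence with sexual distress (FSDS-DAO). Add one sentence saying that FSFI, analysed in the sexually active subset, is not separately powered at d=0.30.

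In the primary objective analyses, where FSFI may lead to removal of a component, add that failure to detect a negative FSFI effect is not evidence from an analysis powered at d=0.30.

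If FSFI figures are given at all, label them illustrative and state the assumed evaluable share, correlation and attrition beside them.

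The cost is a few lines of text and a less favourable claim for a secondary outcome. No patients, assessments or analyses change.

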### Data Analysis Plan

#### Overview

In accordance with the NIH requirement, a Data Safety and Monitoring Plan has been established to guide study oversight and ensure the safety of participants and data validity and integrity. Summaries of primary and secondary measures will be reviewed for completeness every 6 months by the WF NCORP RB Data Safety Monitoring Board, along with other key study metrics such as recruitment, retention, patient characteristics, and adverse events. More details about trial oversight and monitoring are available in Multimedia Appendices 3 and 4.

Study methods have been designed to avoid missing data, including efforts to retain participants with incentives and assessment reminder protocols, as well as requiring responses to all items on web-based assessment questionnaires. As it is not possible to entirely avoid missing data, restricted maximum likelihood estimation will be used to address missing data in analyses under a missing at random (MAR) assumption [63-65]. Proposed analyses are robust against MAR data [63,64]. The National Academy of Sciences guidelines for missing data will be followed [64], and the impact of missing data on study conclusions will be explored with sensitivity analyses. Specifically, attrition rates across study conditions will be compared. If a particular condition has a markedly higher dropout rate, baseline covariates that predict attrition will be identified in secondary analyses. Variables determined to predict loss to follow-up will be included in sensitivity analysis models to satisfy the conditions described by Little and Rubin [65] for data to be considered MAR.

Primary analyses will be intention to treat, meaning that the randomized condition assignment will be included in models regardless of whether the participant completes their assigned Cores or not. Sensitivity analyses will examine the effects by whether assigned Cores are completed or not. All participants with at least 1 follow-up assessment will be included in analyses. All tests of hypotheses and reported P values will be 2 sided.

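### The REML/MAR statement and the at-least-one-follow-up rule do not fit the change-score ANOVA named as the primary model; the model that REML is applied to needs to be stated

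*Protocol article*

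**What the plan says.** Four parts of the protocol article bear on this.

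- **Data Analysis Plan, Overview.** On missing data, "restricted maximum likelihood estimation will be used to address missing data in analyses under a missing at random (MAR) assumption". The next sentence adds: "Proposed analyses are robust against MAR data". On the analysis set: "All participants with at least 1 follow-up assessment will be included in analyses". If one condition has markedly more dropout, baseline covariates that predict attrition are to be sought and added to sensitivity models.
- **Primary Objective Analyses.** Main and interaction effects come from a "generalized linear model (GLM) approach to ANOVA with effect coding to compare the average change in sexual morbidity aggregated across experimental conditions". No time factor, random effect or within-woman covariance is named. Components enter the package provisionally if their main effect reaches d≥0.3.
- **Sexual Morbidity Outcomes.** FSDS-DAO is measured at baseline and weeks 12 and 24, and "the primary evaluation is change between baseline and 24-week assessments". Table 1 lists the 12-week FSDS-DAO as a key secondary outcome.
- **Sample Size and Power Analysis.** 247 women are required for d=0.30 in the baseline-to-week-24 change with a pre-post correlation of 0.65. This is raised to 309 for 20% attrition and rounded to 320.

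**The concern.** REML helps with missing outcomes when a woman contributes several correlated records: her observed visits then carry information about the missing one. An ANOVA of a single change score has no such records. On that reading the Overview promises two things that the model under Primary Objective Analyses cannot deliver: a place in the analysis for women seen at week 12 but not at week 24, and general protection under MAR.

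Dropout that depends on how a woman was doing at week 12 is a MAR mechanism, because the week-12 score is observed. A model that leaves that score out cannot condition on it. The planned sensitivity models do not close the gap. They draw on baseline predictors, and they are triggered by unequal dropout rates; the mechanism can differ between component levels while the rates are similar.

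The stake is the decision rule. Keeping or dropping a component turns on whether a point estimate reaches 0.3, so a shift of about 0.1 SD could change the package.

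**Working it through.** **1. Which outcome was the trial sized for?** Inputs from Sample Size and Power Analysis: d=0.30, r=0.65, and power stated as "at 80% power with α=.05 for all main effects and interaction effects of the intervention components". The Overview makes tests two-sided.

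- SD of a change score in single-visit SD units: √(2(1−0.65)) = √0.70 = 0.837.
- Standardised effect on change: 0.30/0.837 = 0.3586.
- Smallest N with noncentral-t power of at least 0.80, with 16 model terms: **247** (normal approximation 246). This matches the plan.
- Alternatives: baseline as covariate, effect 0.30/√(1−0.65²) = 0.3948, gives 204; no pretest gives 351.
- 247/0.80 = 309, also as stated.

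The sizing is therefore for a two-time-point change contrast, which agrees with the wording under Primary Objective Analyses.

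**2. What does REML do with one record per woman?** With V = σ²I, the estimator (X′V⁻¹X)⁻¹X′V⁻¹y becomes (X′X)⁻¹X′y, which is ordinary least squares. REML changes only the variance estimate, to RSS/(n−p). A woman with no week-24 value has no y and adds nothing. At 20% attrition, 0.20 × 320 = 64 women are lost. The number of these with a week-12 visit is not given, so it lies between 0 and 64.

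**3. Power.** 320 − 64 = 256 records give 81.5% (25% missing: 240 records, 79.0%; 30%: 224 records, 76.1%). Planned attrition is already allowed for.

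**4. Bias.** Simulations used 320 women, a true effect of -0.30 SD, 3,000 to 4,000 trials per scenario and roughly 17–23% missing week 24. Correlations were 0.65 (weeks 0–12), 0.65 (weeks 0–24) and 0.75 (weeks 12–24) unless stated. The two involving week 12, and every dropout mechanism, are assumptions; the documents give none of them. Log-odds are per SD.

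| Dropout before week 24 depends on | Complete-case change estimate |
|---|---|
| 12-week change, equally in both levels (log-odds up to 1.5) | mostly -0.27 to -0.29; -0.26 at the extreme |
| 12-week change, 0.75 v 0.5 or 1.5 v 1.0 by level | about -0.32 |
| 12-week score, 'on' level only, log-odds 1.0 | about -0.32 |
| 12-week score, opposite signs by level (0.8 v -0.8) | -0.30, -0.265, -0.236 for week 12–24 correlation 0.65, 0.75, 0.85 |
| 12-week change, 'on' level only, log-odds 1.0, half the loss unrelated | about -0.355 |
| 12-week change, 'on' level only, log-odds 1.0–1.5, less improved women leave | -0.38 to -0.43 |
| As above, but improvers leave | about -0.16 (runs from -0.18 to -0.13) |

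A likelihood model that uses the week-12 score gave about -0.30 throughout, with a standard error no larger than that of the complete-case analysis (about 0.10).

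**5. Why the rows differ.** What matters is how strongly the driver of dropout is related to the 24-week change.

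- 12-week change: covariance 0.75 − 0.65 − 0.65 + 1 = 0.45; correlation 0.45/0.70 = 0.64.
- 12-week score: covariance 0.75 − 0.65 = 0.10; correlation 0.10/0.837 = 0.12.
- 12-week score with all correlations 0.65: covariance 0, hence no bias.

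Large bias needs dropout driven by 12-week change and a mechanism that differs clearly between component levels.

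**The case against.** The strongest reply is that one record per woman is inferred. The article never says so, and never says that women without week 24 are dropped. REML, MAR, three assessments and the at-least-one-follow-up rule would all fit a repeated-measures model with a 24-week change contrast, and under that model REML does use women seen only at week 12. A sizing formula does not fix the analysis model, and a journal article commonly leaves covariance structure to the full protocol or SAP. This stands as far as it goes: the authors may intend a sound model. But the primary analysis is then misdescribed as an ANOVA of change, and the same sentence needs correcting.

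A second reply is that the larger biases need one-sided dropout of considerable strength, which nothing in the documents supports. That also stands, so the size has to be given as a range.

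Third, the Overview already plans attrition comparisons and sensitivity models. These help with baseline-driven dropout but do not reach dropout driven by week-12 progress.

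A reader might also infer a breach of intention to treat, because women with no follow-up are left out. The article defines that term by assigned condition regardless of Core completion and states its inclusion rule openly. Women with baseline data only add little information on component effects.

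**Conclusion.** The point holds as an inconsistency. The Overview's statements on REML, MAR and inclusion do not follow from the change-score ANOVA under Primary Objective Analyses. If that model is fitted to one change score per woman, the primary analysis is complete-case at week 24 and robustness under MAR is not secured.

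Under the assumed correlations and about 20% missing, the bias on a true effect of -0.30 ranges from near zero (about -0.28 to -0.32, with equal or mildly unequal dependence on 12-week progress) to slightly more than 0.1 SD in either direction (about -0.43 to -0.16, with dependence on 12-week change in one level only). The upper end is large against a 0.3 cut.

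Three stronger readings are not supported:

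- that the MAR claim is false outright: a complete-case change analysis is unbiased under some MAR patterns, such as dropout that depends only on assigned components;
- that the primary analysis is shown to be biased by about 0.1 SD: that figure belongs to the extreme scenarios;
- that the trial loses its planned power: it does not at 20% attrition.

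**What to change.** State under Primary Objective Analyses that the primary model is a linear mixed model, fitted by REML to FSDS-DAO at weeks 0, 12 and 24, with unstructured within-woman covariance and effect-coded components by time, and that the 24-week component contrasts of change from baseline are primary. The Overview's REML sentence and inclusion rule then describe that model correctly. Including women with baseline data only is optional.

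If the change-score ANOVA is kept, withdraw the at-least-one-follow-up sentence and the MAR-robustness claim for it, and say that the analysis uses women with a week-24 value.

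The cost is wording in the protocol and SAP. The 12-week scores are already collected, and the sample size need not change.
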